## 7.2 SECONDARY CRITERIA

**Table 2** Secondary criteria associated with secondary objectives

| Axis 1     |                                                                                                                                                                                                                                                                                                                                                                        |
|------------|------------------------------------------------------------------------------------------------------------------------------------------------------------------------------------------------------------------------------------------------------------------------------------------------------------------------------------------------------------------------|
| Objectives | Examinations: associated measures                                                                                                                                                                                                                                                                                                                                      |
| 1) a) b)   | 
 
- Actigraphy: rhythm amplitude and acrophase
 
- Sleep diary: scores
 
- Diurnal cortisol: salivary cortisol levels
 
- Polysomnography: sleep efficiency and number of awakenings
 
- ISI, PSQI questionnaires: scores
 
                               |
| 2)         | 
 
- Neuropsychological tests: scores
 
- Spatial memory task: scores
 
- fMRI activation (ANT task): task-related BOLD signal (effective connectivity)
 
                                                                                                                              |
| 3)         | 
 
- aMRI: cortical structures (white and gray matter)
 
                                                                                                                                                                                                                                                           |
| 4)         | 
 
- Resting fMRI: dynamic BOLD signal fluctuations (functional connectivity) corrected for cardiorespiratory confounding factors
 
- Post-MRI debriefing questionnaire: scores
 
                                                                                                                    |
| 5) a)      | 
 
- Polysomnography: sleep efficiency and number of awakenings
 
- ISI, PSQI questionnaires: scores
 
- HVLT: scores
 
- Spatial memory task: scores
 
- MRIA: cortical structures (white matter)
 
- STAI, BDI-II questionnaires: scores
 
 |
| 5) b)      | 
 
- Polysomnography: sleep efficiency and number of awakenings
 
- ISI, PSQI questionnaires: scores
 
- CAR and cortisol pre- and post-MRI: salivary cortisol levels
 
                                                                                                                |
| 5) c)      | 
 
- Polysomnography: sleep efficiency and number of awakenings
 
- ISI, PSQI questionnaires: scores
 
- Quality of life questionnaires: scores
 
                                                                                                                                      |
| Axis 2     |                                                                                                                                                                                                                                                                                                                                                                        |
| Objectives | Examinations: associated measures                                                                                                                                                                                                                                                                                                                                      |
| 1) a)      | 
 
- Actigraphy: rhythm amplitude and acrophase
 
- Sleep diary: scores
 
- Diurnal cortisol: salivary cortisol levels
 
                                                                                                                                                               |
| 1) b)      | 
 
- Spatial memory task: scores
 
                                                                                                                                                                                                                                                                                 |
| 1) c)      | 
 
- CAR and cortisol pre- and post-MRI: salivary cortisol levels
 
                                                                                                                                                                                                                                                |
| 2)         | 
 
- Actigraphy: rhythm amplitude and acrophase
 
- Sleep diary: scores
 
- Polysomnography: sleep efficiency and number of awakenings
 
- ISI, PSQI questionnaires: scores
 
                                                                                            |
| 3)         | 
 
- Polysomnography: sleep efficiency and number of awakenings
 
- ISI, PSQI questionnaires: scores
 
- Neuropsychological tests: scores
 
- Quality of life questionnaires: scores
 
                                                                                   |

**Note.** ISI: Insomnia Severity Index; PSQI: Pittsburgh Sleep Quality Index; ANT: Attentional Network Test; HVLT: Hopkins Verbal Learning Test; CAR: Cortisol Awakening Response; BDI-II: Beck Depression Inventory; STAI: State-Trait Anxiety Inventory.

## 8 STUDY PLAN

### 8.1 METHODOLOGY

The ICANSLEEP project is a bicentric longitudinal study.

Data from 25 patients with localized breast cancer treated with chemotherapy will be compared with those from a group of 25 patients not treated with chemotherapy and a group of 25 cancer-free volunteers (control groups), matched for sex, age and years of education (Barbizet scale).

The various evaluations will be carried out as follows:

- At T1: Approximately 1.5 months after surgery and before the start of chemotherapy in the CHI group and before the start of radiotherapy in the NCH group,
- At T2: after a delay of around 6 months, within 2 weeks of the end of chemotherapy for the CHI group, or at a distance from radiotherapy for the NCH group,
- At T3: after a two-week intervention with GVS versus non-effective stimulation (known as SHAM). To assess the effect of GVS, patients will be assigned to either the effective GVS group or the SHAM group (random selection). SHAM stimulation involves using the device but receiving a very low-frequency current that has no effect on the vestibular system. This approach has already been used and validated in the COMETE unit (Caen, [name]) with which we collaborate. All cancer-free volunteer participants will undergo GVS.

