## 4 SUMMARY OF TESTS TO BE PERFORMED

**Table 1** Summary of assessments offered to participants at different stages of the study

| Assessments                                                                                                                                                                                                                                                                                             | Time | Inclusion | T1
Within one month of inclusion and before the start of treatment (chemotherapy or radiotherapy) | T2
6 months after T1 | T3
2 weeks after T2 |
|---------------------------------------------------------------------------------------------------------------------------------------------------------------------------------------------------------------------------------------------------------------------------------------------------------|------|-----------|------------------------------------------------------------------------------------------------------|-------------------------|------------------------|
| Signature of informed consent                                                                                                                                                                                                                                                                           |      | •         |                                                                                                      |                         |                        |
| Sleep complaints and sleep apnea (questionnaires) :
- ISI
- Berlin Questionnaire                                                                                                                                                                                                                  |      | •         |                                                                                                      |                         |                        |
| Quality and physiology of sleep and circadian rhythms
- Questionnaires (home): ISI, PSQI, Horne and Ostberg
- Actigraphy and sleep diary (over the 2 weeks preceding each evaluation period T1, T2 and T3)
- Polysomnography
- Diurnal salivary cortisol
- CAR and cortisol pre-post MRI |      |           | •                                                                                                    | •                       | •                      |

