These studies have shown changes in the sleep's macrostructure in patients treated for breast cancer, but they have several limitations that prevent a precise understanding of the impact of cancer and treatment on sleep. The absence of a control group in several of these studies is the main limitation. Indeed, the presence of a control group with no history of cancer and a group without treatment makes it possible to determine whether changes in sleep architecture are secondary to the cancer itself or to treatment. In addition, the inclusion of heterogeneous populations in terms of age and cancer type may have limited the statistical power of the studies' results, and prevented changes in sleep architecture from being revealed. In addition, no studies have assessed changes in sleep patterns prior to initiation of chemotherapy. PSG also provides detailed information on the macro- and micro-structure of sleep, enabling links to be made with cognitive performance and the detection of potential sleep disorders such as apnea. New studies, more homogeneous in terms of eligibility criteria, but also longitudinal, are needed to determine the presence of sleep disorders in breast cancer patients. A better understanding of these sleep disturbances will also enable to determine their possible contribution to the onset of cognitive and psychopathological deficits.

Patients with breast cancer suffer not only from impaired episodic memory, but also from impaired executive functions. The latter are particularly involved in a particular form of episodic memory, spatial memory, which has so far received little attention in breast cancer. This type of memory enables to remember a route or find objects in different places, and is therefore essential for everyday life. What's more, it relies on the integrity of the hippocampus, a region that appears to be affected in women with breast cancer . Sleep disturbances are also known to impair executive functions involving the prefrontal cortex  and the cognitive control mechanisms that depend on it. These cognitive control mechanisms enable the regulation of behavior in complex situations, particularly after a stressful event. In breast cancer, sleep disorders could have a negative impact on these control mechanisms, leading to reduced resistance to stress.

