## 6 RESEARCH HYPOTHESIS AND EXPECTED RESULTS

##### Axis 1:

- 1)
  - a) Sleep and circadian rhythms would be altered in patients before chemotherapy compared with cancer-free subjects. Chemotherapy would exacerbate these effects compared with the no-chemotherapy group
    - For sleep, more awakenings lasting more than a minute and poorer sleep quality are expected.

- For circadian rhythms, the sleep/wake and cortisol rhythms are expected to be less ample.
- b) Altered rhythms have deleterious effects on sleep quality**
- 2)** Cognitive abilities would be more impaired after than before chemotherapy, whereas no decline is expected in patients not treated with chemotherapy and in healthy subjects. More specifically, this decline is expected to affect:
    - Spatial and episodic memory
    - Working memory
    - Executive and attentional functions
    - Functional connectivity during the ANT (Attentional Network Test) task, particularly within the orientation and cognitive control networks
  - 3)** After chemotherapy, the cortical structure should be altered, particularly in the regions involved in the above-mentioned cognitive abilities (i.e., hippocampus, frontal regions, cerebellum) compared to before chemotherapy, and compared to patients not treated with chemotherapy and healthy subjects.
  - 4)** For both groups of patients, the dynamics of functional connectivity at rest prior to chemotherapy should be altered, with greater ruminations than in the healthy group.
  - 5) a)** Sleep disturbances (independently of the effects of anxiety and depression) are thought to be linked to cognitive abilities and their neuro-anatomical correlates, specifically:
    - Episodic and spatial memory performance
    - White matter structure and functional connectivity
  - b)** Sleep disturbances are also associated with hyperactivity of physiological stress systems
  - c)** Sleep disturbances are associated with a lower quality of life

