##### **In patients not treated with adjuvant chemotherapy (NCH group)**

- The T1 assessment will take place after surgery and before the start of radiotherapy.
- T2 assessment will take place 6 months after T1

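### No patient group is untreated at T2, yet section 5.1 relies on one, and section 12.2 tests a cancer effect at T2 and a chemotherapy effect without a comparator

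*Protocol*

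**What the plan says.** **Rationale.** Section 5.1 criticises earlier studies for lacking controls and states that having cancer-free women and "a group without treatment makes it possible to determine whether changes in sleep architecture are secondary to the cancer itself or to treatment".

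**Timing.** Section 8.1 places T1 "before the start of radiotherapy in the NCH group" and before chemotherapy in the CHI group. T2 is "within 2 weeks of the end of chemotherapy for the CHI group, or at a distance from radiotherapy for the NCH group". Section 8.4.4 repeats this for NCH: "The T1 assessment will take place after surgery and before the start of radiotherapy", and "T2 assessment will take place 6 months after T1". The T1 column of Table 1 (section 4) reads "before the start of treatment (chemotherapy or radiotherapy", so the protocol itself counts radiotherapy as treatment.

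**Hypotheses.** Section 6, hypothesis 1a for Axis 1, expects that "Chemotherapy would exacerbate these effects compared with the no-chemotherapy group". Hypothesis 2 expects no cognitive decline in the patients without chemotherapy.

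**Analysis.** Section 12.2 (Axis 1) assigns two sets of tests. The effect of cancer is assessed by comparing patients with controls at both T1 and T2. The effect of chemotherapy is assessed by comparing T1 with T2 in chemotherapy-treated patients using paired tests. A model of the T2 value adjusted for T1 is offered as an alternative.

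**The concern.** The rationale needs a cancer group whose T1-T2 course carries no treatment effect. The only candidate is NCH, and its radiotherapy lies inside that interval. After T1 the design has two treated patient groups and one cancer-free group.

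Two conclusions are at stake. A difference between patients and cancer-free women at T2 would be reported as an effect of cancer although every patient has by then been treated. A T1-T2 change in the CHI group would be reported as an effect of chemotherapy although, in a test with no comparator, it also contains time, retesting and recovery from surgery and diagnosis. If the alternative model is used instead, any change in NCH caused by radiotherapy is subtracted from the chemotherapy effect, in whichever direction it runs.

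**Working it through.** The protocol gives no figure to reproduce on this point: section 12.1 states that no power calculation was made, and no effect size is given. The check sets out what each planned comparison estimates.

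**Notation**

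- d: difference between patients and cancer-free women at T1, before chemotherapy or radiotherapy (it includes diagnosis and surgery).
- t: T1-T2 change common to everyone (time, retesting).
- k: further T1-T2 change in patients from the course of the disease and recovery from surgery and diagnosis.
- c: effect of chemotherapy at T2, about two weeks after its end (sections 8.1 and 8.4.4).
- r: effect of radiotherapy at T2, at an unspecified distance from it (section 8.1).

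**Assumptions.** NCH patients receive radiotherapy, as the timing rules presume. CHI patients have had none before T2; the protocol does not say whether this is so. k is the same in both patient groups.

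**Expected T1-T2 change**

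| Group | Change |
|---|---|
| CHI | t + k + c |
| NCH | t + k + r |
| CTL | t |

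**What each comparison estimates**

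| Comparison | Place in section 12.2 | Estimates |
|---|---|---|
| Patients vs cancer-free women at T1 | effect of cancer | d |
| Patients vs cancer-free women at T2, patients pooled 25 + 25 | effect of cancer | d + k + (25c + 25r)/50 = d + k + (c + r)/2 |
| CHI, T1 vs T2, paired | effect of chemotherapy, first-named | t + k + c |
| CHI vs NCH, T2 adjusted for T1 or change | possible under the alternative model | (t + k + c) - (t + k + r) = c - r |
| CHI vs CTL, change | not named | k + c |
| NCH vs CTL, change | not named | k + r |

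**Reading the rows**

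1. The T1 row contains neither c nor r, so the T1 comparison is clean of both treatments.
2. The pooled T2 row contains half of each treatment effect. If the patient groups are instead taken separately, the result is d + k + c for CHI and d + k + r for NCH. Neither is an effect of cancer alone.
3. The paired CHI row equals c only if t + k = 0, which the test cannot show.
4. The CHI-NCH row removes t and k and is the better contrast, but it equals chemotherapy against no treatment only if r = 0 at T2. Because c is measured close to the end of treatment and r at a distance, it also mixes type of treatment with time since treatment.
5. The NCH-CTL row mixes k and r. It cannot be assigned to cancer alone or to treatment alone.

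If some CHI patients also had radiotherapy before T2, part of r would enter the CHI row too, and the CHI-NCH contrast would change again.

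**The case against.** The phrase about an untreated group stands once, in a background paragraph, and does not name NCH. The main objective (section 5.4), hypothesis 1a and section 8.1 all name the comparator by the absence of chemotherapy, and sections 4, 8.1, 8.4.2 and 8.4.4 state the radiotherapy openly. For a contrast of chemotherapy with no chemotherapy, radiotherapy is part of the comparator's care. The first-named chemotherapy test does not use NCH, so a change in NCH cannot distort it. Setting NCH's T2 at a distance from radiotherapy may let a transient effect fade. Section 12.2 also describes T1 and T2 by group, so a change in NCH would be visible. No section says that radiotherapy alters sleep.

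Most of this stands, and it limits the point. A reader might infer that the trial fails its declared objective or that CHI-NCH is invalid. The documents do not support that: the failure lies in the section 5.1 rationale and in how section 12.2 labels its tests. A reader might also bring in endocrine therapy, but the protocol does not state it for either patient group; the only hint is the title of a cited study.

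The defence does not cover two things. Labelling the T2 comparison an effect of cancer is operative text. And the first-named chemotherapy test avoids the NCH problem only by having no comparator, although hypothesis 1a is stated against the no-chemotherapy group.

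**Conclusion.** The point holds in this limited form. Section 5.1 conflicts with sections 4, 8.1 and 8.4.4, because no patient group is untreated at T2. Two uses in section 12.2 need correction: the cancer label on the T2 comparison, and the uncontrolled paired test as the first-named assessment of chemotherapy. CHI-NCH is a legitimate contrast if described as chemotherapy versus radiotherapy without chemotherapy, at unequal times since treatment. The T1 comparison of patients with cancer-free women stands.

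The conclusion rests on NCH patients receiving radiotherapy, as the timing rules presume. The form of c - r also assumes no radiotherapy in CHI before T2 and a common course k. A reader might infer a particular loss of power or a percentage by which the chemotherapy effect is understated. The documents support neither: they give no value or sign for r or c, and a shift in NCH in the opposite direction would enlarge the contrast. This is a matter of what the study may conclude, not of its sample size, and it should be corrected before analysis.

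**What to change.** 1. In section 5.1, describe the non-chemotherapy patient group as treated without chemotherapy, so that it agrees with sections 4, 8.1 and 8.4.4.
2. In section 12.2, keep the term effect of cancer (before chemotherapy or radiotherapy) for the T1 comparison of patients with cancer-free women. Describe T2 differences as cancer together with its treatment.
3. In section 12.2, make the main longitudinal analysis of Axis 1 one three-group by time model, or one model of T2 adjusted for T1. Report the CHI-NCH, CHI-CTL and NCH-CTL changes together. Word CHI-NCH as chemotherapy versus radiotherapy without chemotherapy, and attribute the NCH-CTL change neither to cancer alone nor to treatment alone. The paired CHI comparison can stay as description.

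Adjusting CHI-NCH for radiotherapy dates is not recommended: if radiotherapy falls in the interval for NCH only, that covariate nearly coincides with group and the adjusted contrast would be close to inestimable.

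The cost is wording in two sections and one model on data already planned, with no change to visits or care. The downside is a narrower claim for CHI-NCH.

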### 8.2 DURATION OF STUDY

The total duration of the study is 48 months, including a 40-month recruitment period.

The follow-up period for participants is 8 months from the inclusion assessment.

### 8.3 SELECTION OF PARTICIPANTS

For each of the two groups, patients (25 chemotherapy-treated patients and 25 non-chemotherapy-treated patients) will be recruited from the François Baclesse Cancer Center in Caen. Patients not treated with chemotherapy will be of equivalent age and level of education to patients treated with chemotherapy.

A group of 25 female volunteers with no history of cancer, of the same age and level of education as the patients, will be recruited through a call for volunteers (see "Inclusion of cancer-free women" below). Recruitment will take place within Unit 1077 (Caen, France).

#### 8.3.1 Patient inclusion criteria

- Patient aged 45 to 65
- Patient with localized breast cancer, whether or not to start adjuvant chemotherapy
- Patient with education level 3 "end of primary education" (Barbizet scale)
- Patient fluent in French
- Patient having signed consent to participate in the study
- Patient with sleep complaints (ISI > 7)
- Patient with access to the Internet from a home computer

